### Data Privacy and Confidentiality

Confidentiality and privacy of participant data will be restricted to JP. The strategy for identification, coding, and deidentification of participant data will involve recording the participants’ name, email address, and contact phone number in an electronic master list stored at the hospital and retained for archiving purposes. All questionnaires in this study will be delivered using an online encrypted questionnaire platform to ensure participant responses are secure and confidential.

### Data Collection

#### Study Phase 1: Online Australian Diabetes-Specific QoL Questionnaire Development and Piloting

Volunteering participants will consent to completing both the online questionnaire and a face-to-face interview. Table 1 outlines each questionnaire section and provides a brief description of what is included. The participants’ pilot questionnaire link will be active for 2 weeks. A courtesy email reminder will be sent to those who have not completed or have partially completed the pilot questionnaire after 7 days. It is anticipated that the questionnaire will take 10-15 minutes. Once the pilot questionnaire is completed, the participant will be contacted via phone to arrange a suitable time for either a face-to-face interview at the study hospital or an online interview. It is estimated that the duration of the interview will be 20-30 minutes. Interviews will be undertaken by JP with the aid of a question guide to ensure a consistent approach is followed. Each interview will be audio-recorded and then transcribed verbatim. Common participant feedback will be documented and then reviewed by the research team. This feedback will be used to modify specific items identified as needing improved clarity and concision or to remove them due to irrelevance. The revised version of the online questionnaire will be used in study phase 2, and subphases 2a and 2b.

**Table 1 table1:** Study phase 1: online Australian diabetes-specific quality of life questionnaire completed by adults with type 1 diabetes mellitus (n=25-30).

Questionnaire section	Brief description of items	Source
Section 1: information sheet^a^	Overview of the study	N/A^b^
Section 2: screening questions^c^	Assessment of study eligibility	N/A
Section 3: consent form^a^	Signed by participant	N/A
Section 4: Australian diabetes-specific quality of life questions^d^	A 28-item questionnaire containing 4 constructs measuring diabetes quality of life using a 10-point Likert scale from “very strongly disagree to “very strongly agree”	Adapted from [48,57]
Section 5**:** sociodemographic covariates	Data collection: gender, age, height, weight, diabetes duration, occupation, level of education, etc	Adapted from [61-63]

^a^Participant information and consent form are to be completed online.

^b^N/A: not applicable.

^c^Screening questions are to be completed online. The response to each question is yes or no. The questions include the following: “I have type 1 diabetes mellitus,” “I am 18 years or older,” and “I have had type 1 diabetes mellitus for one year or longer.”

^d^Australian diabetes-specific quality of life questions were developed using previously validated questionnaires [48,57]; input will be collected by the research team through one-to-one participant interviews.

#### Study Phase 2: Online Australian Diabetes-Specific QoL Validation

Study phase 2 will be split into 2 subphases (2a and 2b). Study subphase 2a will consist of initial validation using the online Australian diabetes-specific QoL questionnaire. Data will be collected from 364 participants to support the statistical validation of the questionnaire. These 364 participants will be different to those who participated in study phase 1. Table 2 shows each questionnaire section and a brief description of the section. After 7 days, a reminder email will be sent to those participants who have not commenced or have only partially completed the questionnaire. It is anticipated that the questionnaire will take 10-15 minutes to complete. Study subphase 2b will consist of the subsequent validation using the online Australian diabetes-specific QoL, MOS SF-36, DQOL, and PAID-20 questionnaires. All participants (N=364) from study subphase 2a will receive an email 3 months after completing the initial online questionnaire requesting the completion of the questionnaire for a second time. This email will also request the participant to complete the online MOS SF-36 [52], DQOL [49], and PAID-20 questionnaires [53].

**Table 2 table2:** Study phase 2a–initial validation: online Australian diabetes-specific quality of life questionnaire completed by adults with type 1 diabetes mellitus (N=364).

Questionnaire section	Brief description of items	Source
Section 1: information sheet^a^	Overview of the study	N/A^b^
Section 2: screening questions^c^	Assessment of study eligibility	N/A
Section 3: consent form^a^	Signed by participant	N/A
Section 4: Australian diabetes-specific quality of life questionnaire	A 28-item questionnaire containing 4 constructs measuring diabetes quality of life using a 10-point Likert scale from “very strongly disagree” to “very strongly agree”	Adapted from [48,57]
Section 5: sociodemographic covariates	Data collection: gender, age, height, weight, diabetes duration, occupation, level of education, etc	Adapted from [61-63]

^a^Participant information and consent form are to be completed online.

^b^N/A: not applicable.

^c^Screening questions are to be completed online. The response to each question is yes or no. The questions include the following: “I have type 1 diabetes mellitus,” “I am 18 years or older,” and “I have had type 1 diabetes mellitus for one year or longer.”

Participants will be supplied with a link for access to all 4 questionnaires. Of the 364 participants, 100 participants will be needed to complete the questionnaire to establish test–retest, convergent, and divergent validity. Table 3 outlines the questionnaires to be completed as part of the subsequent validation process.

**Table 3 table3:** Study phase 2b–subsequent validation: online Australian diabetes-specific quality of life, MOS SF-36, DQOL, and PAID-20 questionnaires completed by adults with type 1 diabetes mellitus (n=100).

Questionnaire section	Brief description of items	Source
Section 1: information sheet^a^	Overview of the study	N/A^b^
Section 2: screening questions^c^	Assessment of study eligibility	N/A
Section 3: consent form^a^	Signed by participant	N/A
Section 4: Australian diabetes-specific quality of life questionnaire	A 28-item questionnaire containing 4 constructs measuring diabetes quality of life using a 10-point Likert scale from “very strongly disagree” to “very strongly agree”	Adapted from [48,57]
Section 5: MOS SF-36^d^	Measures of physical and psychological constructs of general well-being with varying response scales	[52]
Section 6: DQOL^e^	A 43-item instrument consisting of 4 constructs (satisfaction, impact, social/vocational worry, diabetes-related worry). A Likert response format from “very satisfied” to “not satisfied” for the satisfaction construct and from “never” to “always” for the other constructs.	[49]
Section 7: PAID-20^f^	A 20-item questionnaire that measures diabetes-related distress. Each item addresses a different issue associated with diabetes. A 5-point response scale is used from “not a problem to “serious problem”.	[53]
Section 8: sociodemographic covariates	Data collection: gender, age, height, weight, diabetes duration, occupation, level of education, etc	Adapted from [61-63]

^a^Participant information and consent form are to be completed online.

^b^N/A: not applicable.

^c^Screening questions are to be completed online. The response to each question is yes or no. The questions include the following: “I have type 1 diabetes mellitus,” “I am 18 years or older,” and “I have had type 1 diabetes mellitus for one year or longer.”

^d^MOS SF-36: Medical Outcomes Study 36-Item Short Form Health Survey.

^e^DQOL: Diabetes Quality of Life Measure.

^f^PAID-20: Problem Areas in Diabetes.

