### Study Outline

First, approval for the study was gained from the Gold Coast Hospital and Health Service (GCHHS) HREC and the University of Canberra HREC.

#### Study Phase 1

Study phase 1 will consist of the development and piloting of the online Australian diabetes-specific QoL questionnaire. In all, 25-30 adults (≥18 years old) with T1DM will be included. Data will be collected via an online questionnaire (10-15 minutes) followed by a face-to-face or online interview (20-30 minutes), with the period of data collection lasting 1 month. The face-to-face or online interview location will be the Gold Coast University Hospital, Outpatient Department, Diabetes Resource Centre or the Zoom online platform (the participants may choose their preferred interview method), respectively. Interview data will be audio-recorded, transcribed verbatim, coded, and parsed for common themes. A summary of key suggestions for revising the online questionnaire to be used in study subphases 2a and 2b will be produced.

#### Study Phase 2

Study phase 2a will be the initial validation of the online Australian diabetes-specific QoL questionnaire. In all, 364 adults (≥18 years old) with T1DM will be included. Data will be collected via an online questionnaire (estimated completion time 10-12 minutes). Participants will have access to the questionnaire for 2 weeks. If the questionnaire link expires, the participant may request a new link by contacting JP. The data collection period for this phase will last 3 months.

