Study phase 2b will consist of subsequent validation of the Australian diabetes-specific QoL questionnaire using the MOS SF-36, the DQOL, and the PAID-20 questionnaires. Three months after study subphase 2a is completed, study subphase 2b will commence. Participants from study subphase 2a will be invited by email to complete the same online questionnaire for a second time. In addition, they will be asked to complete the MOS SF-36 [52], DQOL [49], and the PAID-20 [53] questionnaires. Responses will be analyzed to determine the statistical reliability and validity of the Australian diabetes-specific QOL questionnaire. In all, 100 adults (≥18 years old) with T1DM will be included. Data will be collected via an online questionnaire (estimated completion time 15-18 minutes). Participants will have access to the questionnaire for 2 weeks. If the questionnaire link expires, the participant may request a new link by contacting JP. The data collection period for this phase will last 3 months.

#### Study Phase 3

Study phase 3 will comprise preintervention, intervention, and postintervention procedures. The overall aim of this phase is to determine if an association exists between a low carbohydrate diet, QoL, and glycemic control in adults living with T1DM through use of a cross-sectional cohort study. In all, 16-23 adults (≥18 years old) with T1DM will be included.

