#### Study Phase 2: Online Australian Diabetes-Specific QoL Questionnaire Validation

This phase will include 2 subphases: 2a and 2b. Subphase 2a will involve initial validation. This will include the online Australian diabetes-specific QoL questionnaire and will require 364 adult participants with T1DM. This sample size has been calculated using the participant-to-item ratio method [56]. Subphase 2b will involve subsequent validation. This will include the online Australian diabetes-specific QoL, MOS SF-36, DQOL, and PAID-20 questionnaires, and will require 100 responses to be collected for test–retest, convergent, and divergent validity statistical analysis. This sample size is based on biostatistician advice and other studies that have validated QoL instruments [49,57-59].

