#### Phase 3: The Low Carbohydrate Dietary Intervention

Phase 3 is planned to commence in February 2021. Potential participants will volunteer to participate in the study by responding to the contact details of JP on information flyers in the hospital patient waiting areas or provided to them by an endocrinologist or CDE. Potential study participants may include those who participated in study phase 1 or 2 but may also include those who did not necessarily participate in any of the previous study phases. Potential participants who contact JP regarding study participation will have a verbal discussion to ensure they meet the inclusion criteria. Subsequently, the following study requirements for participants will be explained: following a low carbohydrate diet for 12 weeks, using a CGMS for 12 weeks, testing blood ketones weekly, completing a daily food diary, participating in 2 in-person study hospital appointments, and participating in weekly diabetes dietitian and endocrinologist telephone appointments. If the participant provides verbal consent to be included in the study, a preintervention appointment date and time will be organized with the participant to attend the study hospital 1 week prior to commencing the intervention. The participant will be sent an email to confirm the appointment date and time as well as a participant information and a consent form. The consent form may be completed and returned to JP by email prior to or at the preintervention appointment. Two days prior to the preintervention appointment, JP will telephone the participant as a courtesy reminder of the appointment date and time.

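### The test–retest interval for the new QoL questionnaire is stated in two conflicting ways, is at least 3 months under both, and may span the Phase 3 diet, so the coefficient is likely to be biased downward by an unknown amount.

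*Protocol article*

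**What the plan says.** Data Collection (Study Phase 2) sets a clock for each person. All 364 subphase 2a participants are contacted individually, and each "will receive an email 3 months after completing the initial online questionnaire requesting the completion of the questionnaire for a second time".

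Study Outline (Study Phase 2) sets a clock for the phase: "Three months after study subphase 2a is completed, study subphase 2b will commence". It says of 2a, and again of 2b, "The data collection period for this phase will last 3 months". Once a link is sent, "Participants will have access to the questionnaire for 2 weeks", and an expired link can be renewed on request.

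The second completion serves reliability. Study Outline says "Responses will be analyzed to determine the statistical reliability and validity of the Australian diabetes-specific QOL questionnaire", and Sample Size says subphase 2b "will require 100 responses to be collected for test–retest, convergent, and divergent validity statistical analysis".

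Phase 3 gives the same questionnaire before and after a 12-week diet, and the Abstract names QoL change over those weeks as a primary outcome. On who may join, the Phase 3 part of Data Collection says "Potential study participants may include those who participated in study phase 1 or 2". Nothing in the article removes such people from the retest set. The 2b screening questions (footnote to Table 3) cover only diabetes type, age and time since diagnosis. A global impression of change questionnaire is described for Phase 3 only.

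**The concern.** A test–retest coefficient separates measurement error from real differences between people only if each person's true score holds still between the two completions. Where true scores move by different amounts in different people, that movement is booked as error and the coefficient falls.

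Three features make this a live issue here. The interval is long, and no reason for its length is given. Under the Study Outline wording it also differs between people according to when they answered. And some retests could fall during or after a dietary intervention that is studied for its effect on QoL.

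Validation of the questionnaire is primary outcome 2. At stake is whether the published reliability figure describes the instrument, or a mixture of instrument error, natural drift and diet effect over an interval that staff cannot determine from the text.

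**Working it through.** **Step 1. The interval under each wording.** Inputs: 2a collects for 3 months, 2b collects for 3 months, and a link stays open 2 weeks (14/30.44 = 0.46 months).

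- Per-person clock (Data Collection): shortest 3 months; longest 3 + 0.46 = about 3.5 months, the same for everyone (ignoring renewed links).
- Phase clock (Study Outline): 2a runs over months 0–3, and 2b opens at month 3 + 3 = 6 and closes at month 9.
  - Shortest: 6 − 3 = 3 months.
  - Longest if everyone is invited on the opening day and answers within the 2-week link: 6 + 0.46 − 0 = about 6.5 months, with a mean of about 4.7.
  - Longest possible: 9 − 0 = 9 months. The mean is about 6 if answers are spread evenly over both windows.

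The two wordings agree only on the minimum of 3 months. The Phase 3 diet lasts 84 days, and 84/30.44 = 2.8 months, so every retest interval is at least as long.

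**Step 2. What instability does to the coefficient.** The documents give neither a true reliability nor a stability figure for QoL, so both are assumptions. Take true reliability as 0.85, let s be the 3-month correlation of true scores, and let stability decay geometrically:

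expected coefficient at t months = 0.85 × s^(t/3)

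| s (assumed) | 2 weeks | 3 months | 6 months | 9 months |
|---|---|---|---|---|
| 1.00 | 0.85 | 0.85 | 0.85 | 0.85 |
| 0.95 | 0.84 | 0.81 | 0.77 | 0.73 |
| 0.90 | 0.84 | 0.77 | 0.69 | 0.62 |
| 0.80 | 0.82 | 0.68 | 0.54 | 0.44 |

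For example, at 3 months with s = 0.80: 0.85 × 0.80 = 0.68. The loss is nil in the first row. In the other rows a retest at 2 weeks removes most of it.

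**Step 3. Would it show against sampling error?** With n = 100 and a Fisher-z interval, tanh(atanh(r) ± 1.96/√97), the 95% limits are 0.79–0.90 around 0.85 and 0.56–0.77 around 0.68. A loss of that size would be visible. At s = 0.95 the limits around 0.81 are 0.73–0.87, which still include 0.85.

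**Step 4. Uniform change.** If everyone moved by the same d standard deviations, a Pearson correlation would be unchanged, but an agreement ICC would fall to 0.85/(1 + d²/2). For d = 0.3 this is 0.85/1.045 = 0.81.

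**Step 5. Overlap with Phase 3.** Phase 3 recruits at most 23 people, so at most 23 of the 100 retests could be affected. That ceiling requires every Phase 3 recruit to come from Phase 2, to enrol between the two completions, and to be among the 100. It is not a forecast. Overlap is plausible on the calendar: Phase 1 was still recruiting (12 of 25–30), Phase 3 was planned for February 2021, the phase clock makes Phase 2 last 9 months, and all data collection was due to end in March 2022.

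**The case against.** The strongest reply is that Phase 2 participants receive no intervention. Phase 3 looks for change under a prescribed diet with glucose monitoring and weekly calls. A good instrument should be stable without treatment and should move with it. A reader might infer that a questionnaire cannot have a 3-month retest and also detect change over 12 weeks. The documents do not support that. Phase 3 shows only that the authors think 12 weeks is long enough for QoL to change under the diet, not that it drifts without it. This part of the reply stands.

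Three other tempting readings also go too far:

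- *Reliability will be underestimated.* Without a stability figure, a loss of zero cannot be ruled out. Nor does the conflict between the two wordings itself create bias. It leaves the interval undefined and, under the Study Outline, longer and uneven.
- *A sound questionnaire could fail validation.* No retest threshold is stated. Table 4 lists RMSEA, CFI and TLI as the validation indicators, and the initial validation in 2a rests on a single completion that the retest interval does not touch.
- *The coefficient sets the noise level for Phase 3.* The article makes no such use of it. If it did, untreated variation over about 3 months would match a 12-week pre–post comparison better than a short retest.

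It can also be said that the Study Outline sentence is loose drafting, since rolling invitations after a 3-month 2a would themselves fill a 3-month 2b. That is plausible, but its wording refers to the subphase and needs correcting. An article may leave a stability item to the full protocol, so its absence alone is no finding. It matters because the interval that is stated is long and the overlap with Phase 3 is expressly allowed.

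**Conclusion.** The concern stands at moderate weight. Two things follow directly from the text: the retest interval is stated in two incompatible ways, with a minimum of 3 months under both, and people may enter the Phase 3 diet between test and retest and remain in the reliability analysis.

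That the coefficient is likely to be biased downward is a judgement. It rests on QoL changing differently between people over 3 months or more, whether untreated or through the diet. The amount is unknown. On the assumed reliability of 0.85, the 3-month loss runs from nothing at a stability of 1.00 to 0.85 − 0.68 = 0.17 at 0.80, and more if the phase clock is followed. Such a bias is conservative in that it would not make a poor instrument look reliable.

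**What to change.** 1. Make the Study Outline and Data Collection state one interval, counted from each participant's own first completion, with a window. A few weeks is preferable for reliability. If 3 months is kept, justify it and report the result as longer-term stability.
2. Add one item at the retest asking whether the person's situation has changed. Report the ICC in those who say no alongside the ICC in all retested participants.
3. Exclude from the retest set anyone who entered Phase 3 between the two completions.

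The SF-36, DQOL and PAID-20 can stay with the second completion, because the convergent and divergent comparisons use scores collected together.

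The cost is a changed email schedule and one question. The downsides are some recall of first answers at a short interval, a slightly smaller retest set, and a coefficient that no longer describes natural variation over 12 weeks. The change should be made before 2a opens, because a missed short interval cannot be recovered for people who have already answered.

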#### Phase 3: The Low Carbohydrate Dietary Intervention

Phase 3 is planned to commence in February 2021. Potential participants will volunteer to participate in the study by responding to the contact details of JP on information flyers in the hospital patient waiting areas or provided to them by an endocrinologist or CDE. Potential study participants may include those who participated in study phase 1 or 2 but may also include those who did not necessarily participate in any of the previous study phases. Potential participants who contact JP regarding study participation will have a verbal discussion to ensure they meet the inclusion criteria. Subsequently, the following study requirements for participants will be explained: following a low carbohydrate diet for 12 weeks, using a CGMS for 12 weeks, testing blood ketones weekly, completing a daily food diary, participating in 2 in-person study hospital appointments, and participating in weekly diabetes dietitian and endocrinologist telephone appointments. If the participant provides verbal consent to be included in the study, a preintervention appointment date and time will be organized with the participant to attend the study hospital 1 week prior to commencing the intervention. The participant will be sent an email to confirm the appointment date and time as well as a participant information and a consent form. The consent form may be completed and returned to JP by email prior to or at the preintervention appointment. Two days prior to the preintervention appointment, JP will telephone the participant as a courtesy reminder of the appointment date and time.

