**Results:**

Phase 1 of the study is currently open for recruitment and has recruited 12 participants to date. It is anticipated that the first results will be submitted for publication in November 2021. Presently, no results are available.

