## Results

To date, 12 participants have been recruited into phase 1 of this study. The anticipated data collection completion date for all study phases is March 2022. At present, no study results are available.

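### Phase 2a participants may start the Phase 3 diet before their retest and stay in the retest pool, so a few test-retest pairs may span the intervention (minor)

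*Protocol article*

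**What the plan says.** On entry to Phase 3, the Data Collection section (Phase 3: The Low Carbohydrate Dietary Intervention) states: "Potential study participants may include those who participated in study phase 1 or 2". It adds that people from no earlier phase may also join. Nothing makes entry depend on the 2b retest.

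On the retest, the Data Collection section for Study Phase 2 states: "All participants (N=364) from study subphase 2a will receive an email 3 months after completing the initial online questionnaire". It then says: "Of the 364 participants, 100 participants will be needed to complete the questionnaire". The 2b screening questions (Table 3, note c) ask only about having type 1 diabetes, age and duration of diabetes, so a person on the diet would pass them.

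The Study Outline gives the retest a different starting point: "Three months after study subphase 2a is completed, study subphase 2b will commence". For 2a and again for 2b it says: "The data collection period for this phase will last 3 months".

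On dates, the article gives "Phase 3 is planned to commence in February 2021" and "The anticipated data collection completion date for all study phases is March 2022". The abstract reports: "Phase 1 of the study is currently open for recruitment and has recruited 12 participants to date". No start date is given for Phase 2.

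**The concern.** A test-retest coefficient measures reliability only if the respondent's true state is stable between the two occasions. Phase 3 looks for change: primary outcome 3.2 concerns the diet and quality of life, measured with this same questionnaire before and after 12 weeks. If a 2a respondent starts Phase 3 and then completes 2b, any real change enters the reliability estimate as error. An intervention that improves quality of life would then make the instrument look less reliable. Such a person also completes the questionnaire at the preintervention visit, and at the postintervention visit if that comes before the retest, which adds exposure between test and retest.

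Reliability and validity are to be determined in subphase 2b and belong to primary outcome 2. The authors did consider overlap elsewhere, since 2a participants must differ from those in Phase 1. No matching rule separates 2b from Phase 3.

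**Working it through.** **1. Can the diet fit between test and retest?** Phase 3 is 1 lead-in week + 12 diet weeks = 13 weeks (Study Outline, Study Phase 3).

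- *Individual schedule (Data Collection, Study Phase 2).* The invitation goes out 3 months after the person's own first questionnaire: 365.25 / 4 / 7 = 13.0 weeks. If the preintervention visit is s weeks after that questionnaire, the diet weeks completed at invitation are 13 − 1 − s. That is 12 weeks at s = 0, 8 weeks at s = 4 and none at s = 12. The whole diet fits only if entry is almost immediate; later entry gives partial exposure.
- *Phase schedule (Study Outline).* 2b opens 3 months after 2a closes, and each collects for 3 months. The interval runs from about 3 months (last 2a respondent, first day of 2b) to 3 + 3 + 3 = 9 months (first 2a respondent, last day of 2b). For most people there is ample room for all 13 weeks.

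The pair can span the diet on either schedule.

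**2. Do the calendars overlap?** On the phase schedule Phase 2 lasts 9 months, so 2a would have had to open by about May 2020 for 2b to close before February 2021. On the individual schedule it lasts about 3 + 3 + 0.5 (two-week link) = 6.5 months, which gives about mid-July 2020. Before 2a can open, Phase 1 (12 of 25 to 30 recruited when the article was written) must finish and the questionnaire must be revised. The article cites a 2020 patient count and a 2020-numbered ethics approval, so it was written in 2020 or later. Overlap is therefore likely, but the date of writing and the start of 2a are not shown.

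**3. How many pairs?** The plan's maximum for Phase 3 reproduces as 16 × (1 + 0.40) = 22.4, rounded up to 23. (How attrition was applied is a separate matter; the stated cap is what counts here.)

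- Ceiling: 23 of 100 pairs.
- If all 23 came from 2a and answered 2b at the average rate: 23 × 100/364 = 6.3.
- Same, counting only the 16 planned completers: 16 × 100/364 = 4.4.
- If half of the 23 came from 2a: about 3.

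**4. How much reliability is lost?** The article names no coefficient and gives no expected value, so the following are assumptions: agreement-type ICC; true value r = 0.80; baseline variance 1; a fraction p of pairs shifted at retest by a mean d (in SD units) with between-person SD τ, unrelated to starting level.

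Retest variance: v = 1 + pτ² + p(1 − p)d². Mean difference: m = pd. Observed agreement: 2r / (1 + v + m²).

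| Pairs affected of 100 | d = 0.3, τ = 0.3 | d = 0.5, τ = 0.5 | d = 0.8, τ = 0.5 |
|---|---|---|---|
| 6 | 0.796 | 0.788 | 0.779 |
| 23 | 0.784 | 0.757 | 0.726 |

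Worked case, p = 0.06, d = 0.8, τ = 0.5: v = 1 + 0.0150 + 0.0361 = 1.0511; m² = 0.0023; 1.6 / 2.0534 = 0.779.

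**5. Against sampling error.** The approximate 95% interval for 0.80 with n = 100 (Fisher z, standard error 1/√97) is 0.72 to 0.86.

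**The case against.** The strongest objection is that this is small, conservative and perhaps hypothetical. At 6 pairs the loss is at most about 0.02, well inside the sampling interval, and it understates reliability rather than flattering the instrument. All of that stands. It is also fair that a journal article condenses the full protocol, where the rule defining the test-retest set may appear. The point nevertheless rests on two rules the article does state, open entry to Phase 3 and re-invitation of all 364, which together allow the contamination.

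A reader might draw four stronger conclusions that the documents do not support:

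- *That the phases are scheduled to overlap.* March 2022 is only an end date for all phases, Phase 2 has no start date, and the Phase 3 text speaks of earlier phases as previous ones. A sequence is suggested, though no rule enforces it.
- *That Phase 2 needs at least nine months and the retest also lands at the end of the diet.* The nine months come from the phase schedule and the 13-week match from the individual schedule. The two cannot be combined.
- *That 23 of 100 pairs is a working estimate, or that Phase 3 volunteers will be over-represented among responders.* The 23 requires every Phase 3 participant to come from 2a, enter in time and answer 2b. Phase 3 also recruits through flyers, endocrinologists and educators, adds five eligibility criteria and plans for 40% attrition. The selection-bias remark in the Discussion concerns motivation to improve glycemic control, not response to a survey.
- *That the entry and re-invitation rules contradict each other, or that the problem persists at any retest interval.* Both rules can be followed at once; the difficulty is their combined effect. With a two-week interval, the one-week lead-in would leave at most about one week of diet.

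**Conclusion.** The point holds as a minor one. Following the stated rules, some test-retest pairs may span all or part of the Phase 3 intervention, on either retest schedule. Overlap is permitted and likely, not certain. The ceiling is 23 of 100 pairs, with about 6 or fewer more realistic. The loss of ICC is then about 0.00 to 0.02, and 0.02 to 0.07 at the ceiling, in the direction of understating reliability. These losses rest on assumed values for the true ICC and the shift, none of which the article supplies, and on a shift unrelated to starting level. At the realistic count, no conclusion about the instrument is likely to change. It is still worth correcting, because the bias runs one way, affects part of a primary outcome, and would not shrink with more retests if the affected share stayed the same.

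**What to change.** In Data Collection, Study Phase 2, state that any 2a participant who attended a Phase 3 preintervention visit before completing the 2b retest is left out of the test-retest set but kept in the convergent and divergent validity analyses, which do not need a stable state between two occasions. These people can be identified from the electronic master list described under Data Privacy and Confidentiality. The same edit should reconcile the two retest schedules (Study Outline and Data Collection), although the exclusion works under either.

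The cost is one sentence and one check against the list. At most 23 of 364 become unavailable, leaving at least 364 − 23 = 341 from whom 100 retests are needed. Entry to Phase 3 and its conduct are unchanged.
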